### Statistical analysis

Baseline characteristics of both groups will be compared to assess the adequacy of the randomization. Data will be analyzed on an intention-to-treat basis. In addition, a per-protocol analysis will be performed. Trial results will be published in a respective journal. Primary and secondary outcomes for the intervention and control groups will be compared.

The primary outcome CCI will be described as the mean plus the standard deviation (SD). Since we expect CCI to be right skewed we will also describe CCI as the median plus interquartile range (IQR) and percentage above 20. To test the hypothesis (H0) that the study arms result in similar CCIs (in other words, prehabilitation does not prevent postoperative complications), we will use the Student’s T-test if data are normally distributed. Mann-Whitney U if data are not normally distributed or statistical methods that take into account the possible zero-inflated nature of the data. The second primary outcome 6MWT is a continuous variable. This data will be stated as means, plus SD, at each time point. To accommodate the repeat measurements for individuals, we will use a generalized linear mixed model to statistically test the hypothesis of both study arms being equal in terms of functional capacity over time.

All secondary outcomes will be described as means plus SD or median plus IQR, with the data being continuous, and measures for each time point being normally and non-normally distributed respectively. Categorical parameters will be described as number plus percentage per time point. Statistical methods will include t-test and the Mann-Whitney U test for continuous parameters, distributed either normally or not normally respectively, at a single postoperative time-point. Categorical outcomes will be analyzed with Chi-square testing or regression analysis (logistic, ordinal or nominal, depending on the definition of the parameter) for single time points. The size of the sample will be calculated on the basis of the primary aim: the reduction of postoperative complications as determined with the CCI score. With our population variables, the CCI mean is 10.4 (SD 14), and the target reduction is 30%. We use an alpha of 0.05 and power of 0.80 (two-sided test). We expect a dropout rate of 10%. We therefore need 714 patients: 357 in each arm. This gives us sufficient statistical power to demonstrate the expected proportion of difference (55% versus 20%) in the 6MWT between baseline and surgery based on previous studies [14, 27]. Approximately 600 eligible CRC patients undergo surgery in one of the six participating hospitals annually. This implies that we will complete inclusion within two years with the inclusion period being followed by a year of follow-up.

Due to limited clinical data regarding effect size of the primary endpoint – CCI - an interim analysis will be performed. The interim analysis is planned if half of the intended number of subjects have completed the 4 week assessment (i.e. timing of the primary endpoint assessment). The intention of the interim analysis is to terminate the study if there is a statistical significant difference between study arms.

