Since it has been established that the number and severity of complications are closely related to preoperative functional capacity, nutritional status, smoking behavior and psychological well-being, there has been increasing interest in targeting these issues with a multimodal intervention program [15]. From a physiological point of view and based on limited practical experience, it seems feasible to achieve clinically relevant effects during the period of 4–5 weeks between diagnosis and operation [14, 15, 27]. However, this can only be achieved with targeted interventions that include exercise, nutrition, stopping smoking, and psychological support.

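### The tests named for the primary CCI comparison use no baseline covariates, although the protocol records factors it regards as prognostic; the cost is some precision, not validity

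*Protocol article*

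**What the plan says.** The Statistical analysis section of the protocol article gives three routes for testing CCI. Two are named: "we will use the Student’s T-test if data are normally distributed. Mann-Whitney U if data are not normally distributed". The sentence then continues: "or statistical methods that take into account the possible zero-inflated nature of the data". No covariate is attached to any of the three, and no other section names one for CCI.

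The same section says: "Baseline characteristics of both groups will be compared to assess the adequacy of the randomization". For CCI, that is the only analytic role given to baseline characteristics. The second primary outcome differs, because the 6MWT is compared with its own baseline and modelled over time.

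The Background states that "the number and severity of complications are closely related to preoperative functional capacity, nutritional status, smoking behavior and psychological well-being", and the Abstract says much the same. Table 1 places the 6MWT, PG-SGA, GAD-7 and PHQ-9 in the baseline (t0) column. The Smoking cessation section says that past and current smoking is taken by questionnaire but gives no time point, and Table 1 has no smoking entry.

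**The concern.** CCI has no baseline value of its own, so any gain in precision must come from other prognostic variables. The protocol's rationale names such variables, and its schedule collects most of them before prehabilitation starts. A t-test or Mann-Whitney U leaves whatever they explain in the error term. Comparing the arms at baseline does not recover it: that comparison neither narrows the confidence interval nor adjusts the estimate for an imbalance it happens to reveal.

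At stake is the width of the interval around the primary result, in a trial whose planned power has little reserve and whose authors say that clinical data on the effect size are limited.

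**Working it through.** **Inputs**, all from the Statistical analysis section:
- "the CCI mean is 10.4 (SD 14), and the target reduction is 30" percent, so the target difference is 0.30 × 10.4 = 3.12 points, or 3.12/14 = 0.223 SD.
- "We use an alpha of 0.05 and power of 0.80 (two-sided test").
- "We expect a dropout rate of 10" percent.
- Stated size: 714 patients, 357 per arm.

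**The plan's own figure.** For an unadjusted comparison of two means, n per arm = 2 × 14² × (1.96 + 0.842)² / 3.12², which rounds up to 317. Dividing by 0.90 gives 353 per arm, 706 in total. The stated 714 is about 1% above this, so it is reproduced as an unadjusted two-sided calculation on the raw SD of 14.

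**Power of the unadjusted test.** Evaluable patients: 357 × 0.90 = 321 per arm. SE = 14 × √(2/321) = 1.105. Power = Φ(3.12/1.105 − 1.96) = 0.806; the opposite tail is negligible.

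**Power with adjustment.** If the baseline covariates jointly explain a fraction R² of the variance of CCI, the residual SD is 14 × √(1 − R²) and SE = 14 × √(2(1 − R²)/321). The protocol gives no R², so the values below are assumptions. The last column repeats the sample-size calculation with the residual SD, 80% power and 10% dropout.

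| Assumed R² | Residual SD | Power at 321 per arm | Total N for 80% power |
|---|---|---|---|
| 0 (as planned) | 14.00 | 80.6% | 706 |
| 0.02 | 13.86 | 81.4% | 690 |
| 0.05 | 13.65 | 82.6% | 670 |
| 0.10 | 13.28 | 84.5% | 634 |
| 0.20 | 12.52 | 88.4% | 564 |

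The gain is therefore 0.8 points at R² = 0.02, 2.0 at 0.05, 3.9 at 0.10 and 7.8 at 0.20. A gain of 5 points needs R² of about 0.13, a multiple correlation of about 0.36.

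**Limit of the calculation.** It concerns a linear comparison of means, which is what the sample size was based on. It does not measure the loss relative to Mann-Whitney U, the test named for non-normal data.

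**Which covariates are available.** Baseline timing is explicit for the 6MWT, PG-SGA, GAD-7 and PHQ-9. For smoking it is an inference: Study objectives lists smoking status as a secondary outcome, and Study outcomes says that all secondary outcomes are measured at baseline. That sentence cannot be taken literally, since it would also cover length of stay, and the outcome list just before it omits smoking.

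**The case against.** The strongest reply is that nothing stated is wrong. An unadjusted randomised comparison is unbiased, its confidence interval already allows for chance imbalance, and it reaches the planned power. This stands in full. A reader might infer that the CCI result would be biased, or the trial too small; the documents support neither. Stratification by site, tumor location and neoadjuvant treatment also balances some factors by design.

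Second, the zero-inflated option could carry covariates, and the authors expect CCI to be skewed, so the t-test may never be used. It would be too strong to say that the plan excludes adjustment. It leaves one route open but names no covariate for it, while the two tests it does name cannot use any. A condensed article may leave a covariate list to a fuller document. Here, though, the article names the primary tests, and an analysis plan that followed either of them would be unadjusted.

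Third, the covariates may predict less than the Background suggests. That statement concerns preoperative status, whereas the t0 values precede a four-week programme meant to change these factors: more than 20 m on the 6MWT, and a goal of 80% smoking cessation. The Discussion is also more guarded and allows that the factors only may be associated with complications. The statements concern complications rather than CCI itself, although CCI is built from them. This stands, and it argues for the low end of the R² range.

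Finally, a reader might infer that baseline data serve no purpose beyond checking the randomisation. That holds for CCI only, given how the 6MWT is analysed.

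**Conclusion.** The point holds as a modest gain in efficiency, not as an error. The named tests leave unused several baseline measurements that the protocol itself treats as prognostic. If these explain 5% to 10% of the variance of CCI, adjustment raises power by about 2 to 4 percentage points, with no extra patients and no new measurements. At 2% it adds less than one point. Nothing in the documents supports an R² of 0.13 or more, and a skewed score with many possible zeros, measured after a four-week intervention, makes a small value plausible. The conclusion rests on the plan's mean, SD, target reduction and dropout, on a linear model for the mean, and on an assumed R².

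**What to change.** Prespecify the primary CCI analysis as a covariate-adjusted comparison suited to the skew. Two options are linear regression of mean CCI with robust standard errors, or a two-part model standardised to give a difference in mean CCI. The model would contain arm and a short fixed list of values recorded before prehabilitation: baseline 6MWT, PG-SGA, GAD-7 or PHQ-9, and smoking if it is confirmed to be recorded at baseline. State a simple rule for missing baseline covariates so that no patient is dropped. Keep the unadjusted test as a sensitivity analysis.

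The cost is analysis wording only. The small downside is that the covariate list must be fixed in advance, before outcome data by arm are seen; because the protocol plans an interim analysis at the halfway point, that means before the interim.

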Sport physician	–	Informed consent VO2max Anaerobic threshold Exercise-ECG	VO2max Anaerobic threshold Exercise-ECG	–	VO2max Anaerobic threshold Exercise-ECG	–	–
Physiotherapist	–	6MWT Stair climb test Sit-to-stand test 1-RM Activity questionnaire Fried Frailty Score	6MWT Stair climb test Sit-to-stand test Activity questionnaire	–	6MWT Stair climb test Sit-to-stand test Activity questionnaire	6MWT Stair climb test Sit-to-stand test Activity questionnaire	–
Dietician	Food diary	Height, weight Weight loss %^a^ Anthropometry Hand grip strength PG-SGA	Food diary Height, weight Weight loss %^a^ Anthropometry Hand grip strength PG-SGA	–	Height, weight Weight loss %^a^ Hand grip strength PG-SGA	Height, weight Weight loss %^a^ Wrist/abdominal/ Hand grip strength PG-SGA	–
Psychologist	–	Intake Coping with anxiety^c^	–	–	–	–	–
Anesthesiologist	–	–	Preoperative screening^b^	ERAS^b^	–	–	–
Surgeon	–	–	ERAS**	–	–	–	–
Surgical resident	–	–	–	–	Outpatient data	–	–
Researcher	–	HRQoL GAD-7 PHQ-9	HRQoL GAD-7 PHQ-9	–	30-day morbidity and mortality HRQoL GAD-7 PHQ-9	HRQoL GAD-7 PHQ-9	Mortality HRQoL GAD-7 PHQ-9

^a^weight loss in the past 3–6 months. ^b^Following Enhanced Recovery After Surgery (ERAS) guidelines. ^c^when indicated, as stated in the protocol

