### Study outcomes

The initial primary outcome will be postoperative complications, as scored by the Comprehensive Complication Index [39], with the relevant data being collected as a continuous variable and calculated using the sum of morbidity and mortality presented on the Clavien Dindo classification [40]. The CCI score will be calculated at the 30 days of follow-up. The second primary outcome will be the 6MWT measured at 4 weeks after surgery and compared to baseline. The 6MWT will additionally be measured directly after prehabilitation and 8 weeks after surgery.

Secondary outcomes will include patient reported outcome measurements (PROMs) such as health related quality of life (HRQoL) (EORTC QLQ-CR29 and EORTC QLQ-C30 and RAND questionnaires) and depression and anxiety scores (GAD-7, PHQ-9 questionnaires), functional capacity (CPET including VO2max, VO2peak, AT, the sit to stand test, stair climb test, hand grip strength and activity questionnaire), nutritional status (3-day food diary, PG-SGA, anthropometry), postoperative complications, length of hospital stay, study compliance, patient satisfaction and a cost-effectiveness analysis. All secondary outcomes are measured at baseline, the week before surgery, 4 and 8 weeks and 1 year post-surgery.

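### Continuous secondary outcomes with a recorded baseline are assigned unadjusted single-time-point tests, and the visits claimed for all secondary outcomes disagree with Table 1

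*Protocol article*

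**What the plan says.** **Analysis.** In the protocol article, Statistical analysis, the methods for continuous secondary outcomes are the "t-test and the Mann-Whitney U test for continuous parameters, distributed either normally or not normally respectively, at a single postoperative time-point". No baseline covariate, change score or repeated-measures model is named for them. For the second primary outcome, the 6MWT, the same section says "To accommodate the repeat measurements for individuals, we will use a generalized linear mixed model". That model is tied to the 6MWT only, and its covariates are not listed.

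**Visits.** Study outcomes states: "All secondary outcomes are measured at baseline, the week before surgery, 4 and 8 weeks and 1 year post-surgery". Table 1, under Study outline, gives a different schedule. The sport physician's CPET entry ("VO2max Anaerobic threshold Exercise-ECG") appears at baseline, preoperatively and at 4 weeks. The physiotherapist's tests start at baseline ("6MWT Stair climb test Sit-to-stand test 1-RM Activity questionnaire Fried Frailty Score"), and the stair climb, sit-to-stand and activity questionnaire continue to 8 weeks. Among the listed assessments, only the researcher's row has entries at 1 year.

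**The concern.** Patients differ from one another on quality-of-life scores, fitness, strength and nutritional status before any intervention, and part of that difference persists to follow-up. A two-sample test at one postoperative visit leaves this part in the error term and leaves any chance imbalance at baseline uncorrected. The information needed to remove it is already scheduled. The article's reason for modelling the 6MWT, repeated measurement of the same person, applies equally to these outcomes.

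The visit sentence matters for a different reason. It tells the reader that 1-year results will exist for all functional and nutritional outcomes, and 8-week results for CPET and the food diary. The article's own schedule does not collect them. Anyone writing the analysis plan or the results paper from the text alone would list comparisons that cannot be made.

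**Working it through.** **1. The plan's own figure.** The sample size rests on the Comprehensive Complication Index (CCI): mean 10.4, SD 14, 30% reduction (3.12 points), two-sided alpha 0.05, power 0.80, dropout 10% (Statistical analysis).

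n per arm = 2 × (1.960 + 0.842)² × 14² / 3.12² = 317 after rounding up. Dividing by 0.90 gives 353 per arm, 706 in total, against the stated 357 and 714. The difference is about 1%, so the figure reproduces. The CCI has no baseline value, so nothing below changes it.

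**2. Which outcomes have a baseline.** From Table 1, the baseline column holds HRQoL, GAD-7, PHQ-9, CPET, stair climb, sit-to-stand, activity questionnaire, hand grip and PG-SGA, and each is repeated after surgery. Length of stay and postoperative complications have no baseline.

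**3. Cost of leaving baseline out.** With correlation rho between baseline and follow-up, a linear model with baseline as covariate multiplies the variance of the arm difference by 1 − rho². The equivalent sample is 1/(1 − rho²). If the unadjusted test has 50% power, the adjusted power is 1 − Φ(1.96 − 1.96/√(1 − rho²)). The article gives no rho, so a range is assumed.

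| rho (assumed) | 1 − rho² | Variance cut | Equivalent extra patients | 50% power becomes |
|---|---|---|---|---|
| 0.3 | 0.91 | 9% | 10% | 54% |
| 0.5 | 0.75 | 25% | 33% | 62% |
| 0.7 | 0.51 | 49% | 96% | 78% |

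**4. The same loss at the trial's size.** Evaluable per arm: 357 × 0.90 = 321. The smallest difference detectable with 80% power is (1.960 + 0.842) × √(2/321) = 0.221 SD for the plain t-test. Multiplying by √(1 − rho²) gives 0.211, 0.192 and 0.158 SD for rho 0.3, 0.5 and 0.7. For an illustrative effect of 0.20 SD, power is 72% unadjusted and 76%, 83% and 94% adjusted.

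**5. Visits side by side.** Study outcomes claims baseline, preoperative, 4 weeks, 8 weeks and 1 year for every row below.

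| Outcome | Visits in Table 1 | Claimed but not scheduled |
|---|---|---|
| HRQoL, GAD-7, PHQ-9 | all five | none |
| CPET | baseline, preoperative, 4 weeks | 8 weeks, 1 year |
| Stair climb, sit-to-stand, activity questionnaire, hand grip, PG-SGA | baseline to 8 weeks | 1 year |
| Food diary | before start, preoperative | 4 weeks, 8 weeks, 1 year |

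The 1-year column holds only mortality, HRQoL, GAD-7 and PHQ-9. The section on nutritional assessment agrees with Table 1: it places postoperative PG-SGA at 4 and 8 weeks. The blanket sentence also cannot apply to length of stay or postoperative complications, which do not exist before surgery.

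**The case against.** The best defence of the analysis text is that it is a condensed article. The sentence lists what the methods include, which is not exhaustive. The phrase about a single postoperative time-point can be read as limiting these tests to outcomes assessed once, such as length of stay. Covariates are commonly left to a statistical analysis plan, and that plan is not shown. This stands in part: a reader might infer that the protocol commits to a separate unadjusted test at every visit, or rules out baseline adjustment, and it says neither. What remains is that the only comparisons named for continuous secondary outcomes are unadjusted, while the repeated-measures model is given to the 6MWT alone. If the narrow reading is intended, the repeatedly measured outcomes have no stated comparison. Either way the sentence needs changing.

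A second objection is that unadjusted tests are legitimate. That stands fully. Under randomization they are unbiased on average and do not inflate the type I error, so a reader should not infer invalid results.

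A third is that the gain is uncertain. Surgery and complications intervene between baseline and follow-up and may weaken the correlation; at 0.3 the gain is small. The formula also compares linear models and does not measure the gain over a Mann-Whitney test. Both limits stand.

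Nothing comparable answers the visit mismatch. Its reach should not be overstated, though: a reader might infer that no 8-week functional data are collected, but in Table 1 the stair climb, sit-to-stand, activity questionnaire and hand grip do have an 8-week visit. Of the outcomes tabulated above, only CPET and the food diary lack one.

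**Conclusion.** Both parts hold, at moderate weight. The analysis part is a matter of efficiency: a better method is available from data already scheduled. Its size depends on a correlation that the documents do not give, and runs from minor at 0.3 to nearly half the variance at 0.7. It concerns only continuous secondary outcomes with a baseline value. It does not touch the CCI comparison or the sample size.

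The visit part needs no assumption. The Study outcomes sentence and Table 1 cannot both be right for CPET, the physical tests, hand grip, PG-SGA or the food diary.

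**What to change.** 1. For each continuous secondary outcome with a baseline value, specify ANCOVA or a mixed model with the baseline value and the randomization strata (site, tumor location, neoadjuvant treatment) as covariates, and read the arm difference at each scheduled visit. Write the covariates out, since the 6MWT text names none to borrow.
2. For clearly skewed outcomes, use a transformation, or a rank-based or ordinal analysis that still adjusts for baseline.
3. Keep the simple tests for outcomes without a baseline, such as length of stay.
4. Replace the blanket sentence in Study outcomes with outcome-specific visits that agree with Table 1.

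The cost is revised wording and some additional model fits. No extra data or patients are needed. The text would no longer claim 1-year functional or nutritional results, 8-week CPET, or a postoperative food diary.

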### Randomization

Patients will be block randomized with a 1:1 allocation by means of randomization software (Research Manager clinical trial data management system, Deventer, the Netherlands), stratified by study sites, tumor location and neoadjuvant treatment. Patients will be allocated either to the intervention group, which will receive 4 weeks of prehabilitation, or to the control group, which will receive no prehabilitation.

In all participating centers, both the investigator and the surgeon responsible will verify eligibility. If the indication for surgery is established, patients will be screened by the medical research team for health conditions that prohibit participation in the program. They will then be called by the research investigator and an appointment will be made to provide written and oral information about the trial during a scheduled outpatient appointment. Patients will be given enough time to enquire about the details of the trial and to decide whether or not they wish to participate. Patients will be required to sign the informed consent form in the presence of the surgeon or investigator. A participant flow diagram is shown in Fig. 1. After the study has been explained and consent is obtained, there will be a multidisciplinary assessment. Based on intake by the sports physician, the physiotherapist/kinesiologist, the nutritionist and the case manager/psychologist, an individual prehabilitation program will be started during four weeks in the intervention group.

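### The interim stopping rule rests on significance with only an unadjusted two-sided 0.05 in the plan; followed as written, the type I error for CCI is about 8%, not 5%

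*Protocol article*

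**What the plan says.** Everything on this point is in the Statistical analysis section of the protocol article.

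- **Design level:** "We use an alpha of 0.05 and power of 0.80 (two-sided test".
- **Planning values:** "the CCI mean is 10.4 (SD 14), and the target reduction is 30" per cent, with 10% dropout. The result: "We therefore need 714 patients: 357 in each arm".
- **Reason for an interim look:** "Due to limited clinical data regarding effect size of the primary endpoint – CCI - an interim analysis will be performed".
- **Timing:** "The interim analysis is planned if half of the intended number of subjects have completed the 4 week assessment".
- **Decision rule:** "The intention of the interim analysis is to terminate the study if there is a statistical significant difference between study arms".

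The article gives no interim significance level, no boundary and no reduced level for the final test.

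**The concern.** The article does more than announce an interim analysis. It fixes the number of looks (one before the end), the timing, the purpose (stopping on a difference between arms) and the criterion (statistical significance). The only level in the article that gives that criterion a meaning is 0.05. Testing the same endpoint at 0.05 at the interim and again at the end gives two chances of a false positive, so the overall error exceeds the stated 5%.

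Two things are at stake. A positive CCI result could be claimed at a higher error rate than the plan states. A trial stopped at the interim on p<0.05 would also tend to report too large an effect, because only estimates at or near the planned effect, or above it, cross that line with so few patients.

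**Working it through.** **Inputs.** Control mean 10.4, SD 14 and a 30% reduction give a difference of 0.30 × 10.4 = 3.12 points. Two-sided alpha 0.05, power 0.80, dropout 10%, 1:1 allocation (Randomization section).

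**1. The plan's own figure.** n per arm = 2 × SD² × (1.960 + 0.842)² / difference².
- Difference 3.12: 392 × 7.849 / 9.734 = 316.1, so 317; 317 / 0.9 = 352.2, so 353 per arm (706 in total).
- Difference rounded to 3.1: 392 × 7.849 / 9.61 = 320.2, so 321; 321 / 0.9 = 356.7, so 357 per arm, or 714 exactly.

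The 714 is a fixed-sample calculation with the full 0.05 and no allowance for an interim test. Evaluable patients: 321 per arm, 642 in total.

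**2. Information at the interim.** Half of the evaluable patients is 160.5 per arm, information fraction 0.50. Read literally, the trigger is half of 714, that is 357 completers or 178.5 per arm, and 357 / 642 = 0.56. Both are carried forward.

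**3. Type I error with 0.05 at both looks.** Error = 1 − P(|Z1| < 1.96 and |Z2| < 1.96), with Z1 and Z2 bivariate normal under the null and correlation equal to the square root of the information fraction.

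| Information at interim | Type I error |
|---|---|
| 0.40 | 8.6% |
| 0.50 | 8.3% |
| 0.56 | 8.1% |
| 0.60 | 8.0% |

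A simulation at half information with a zero-inflated, skewed outcome (mean 10.4, SD 14) gave 8.4%, so the result does not depend on normality.

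**4. Sensitivity to an interim level that the article does not state.** At half information, p<0.001 at the interim with 0.05 at the end gives 5.02%; p<0.0052 with 0.05 at the end gives 5.2%. The possible range is therefore about 5.0% to 8.3%.

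**5. Early stopping under the planned effect, 0.05 at the interim.** SE = 14 × √(2/n); mean Z = 3.12 / SE; P(stop) = P(Z > 1.96), the opposite tail being negligible; mean estimate if stopped = 3.12 + SE × φ(1.96 − mean Z) / P(stop).

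| n per arm | SE | Mean Z | P(stop) | Mean estimate if stopped | Overstatement |
|---|---|---|---|---|---|
| 160.5 | 1.563 | 1.996 | 51% | 4.33 | 39% |
| 178.5 | 1.482 | 2.105 | 56% | 4.17 | 34% |

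**6. Boundaries that keep 5% overall (one look at half information).**

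| Rule | Interim p | Final p | Power at 321 per arm | Total N for 80% power |
|---|---|---|---|---|
| Single look | none | 0.05 | 80.6% | 706 |
| O'Brien-Fleming | 0.0052 | 0.0480 | 80.3% | 710 |
| Haybittle-Peto | 0.001 | 0.0498 | 80.6% | 706 |
| Pocock | 0.0294 | 0.0294 | 76.3% | 780 |

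With a cut-off of p<0.0052, early stopping under the planned effect is 21% at 160.5 per arm and 24% at 178.5. If the O'Brien-Fleming limits are recalculated for 0.56 (same error formula, interim limit = final limit / √0.56), they become about p<0.0078 and p<0.0471, with 29% early stopping and 80.2% power.

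**The case against.** The strongest reply is that the article never assigns 0.05 to the interim test. The level belongs to the sample-size calculation, and the interim sentence says only that the difference must be significant. Exact boundaries are commonly left to an analysis plan or monitoring charter, neither of which is shown. Nor does a fixed-sample 714 prove that the interim is unadjusted, since O'Brien-Fleming and Haybittle-Peto rules need almost no extra patients. All of this stands, and it makes the 8% conditional. It does not remove the point, because the article does not leave the rule open: it publishes a stopping criterion that, read with the only level given, does not protect the stated 5%.

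Three stronger readings are tempting and are not supported:

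- **That the trial's actual type I error is 8.3%.** A strict interim level in an unseen plan would bring it close to 5%.
- **That the outcome triggering the stop is unstated.** The stopping sentence names none, but the same paragraph justifies the look by CCI and times it by that endpoint's assessment. CCI is the natural reading.
- **That the six-minute walk, 1-year, subgroup and cost results would rest on half the planned patients.** With 10% dropout, 357 completers need about 357 / 0.9 = 397 randomised. Assuming even recruitment over two years (714 / 104, about 7 a week) and 8 to 9 weeks from inclusion to the 4-week visit, another 55 to 62 would already be enrolled. That is about 63 to 64% of 714. Nothing in the article says their follow-up would end.

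**Conclusion.** The point holds as a conditional one. Followed as written, with 0.05 at both looks, the interim rule gives a type I error for CCI of about 8.1 to 8.3% against the stated 5%. Under the planned effect, stopping early is roughly an even chance (51 to 56%), and the effect reported after a stop is too large by 34 to 39% on average.

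These figures assume that significance means two-sided p<0.05 at each look, that the difference is 3.12 with SD 14, and that 321 patients per arm are evaluable at the end. They concern CCI alone; the second primary outcome is not included. The rule should be settled before any interim data are seen, since a boundary chosen afterwards cannot restore error control.

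**What to change.** Before any interim data are seen, state in the protocol or analysis plan an alpha-preserving boundary for CCI and the matching final level. Two options fit within 714 patients at about 80% power:

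- O'Brien-Fleming type: two-sided p<0.0052 at the interim and p<0.048 at the end, recalculated for the information fraction actually reached.
- Haybittle-Peto: p<0.001 at the interim and about p<0.0498 at the end.

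The choice between them is the sponsor's. A Pocock rule would need about 780 patients. If an analysis plan already holds such a boundary, citing it is enough. A short statement that CCI alone triggers stopping would be a useful clarification, no more.

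**Cost.** A sentence or two of text and no added patients. With O'Brien-Fleming limits, power falls from 80.6% to 80.3%. The real downside is a smaller chance of stopping early if the planned effect is true: about 21 to 24% with p<0.0052, or 29% with limits recalculated for 0.56, in place of 51 to 56%.
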